### Measurements in the effect evaluation

#### Primary outcome variables

The primary outcomes of the effect evaluation are psychosocial attributes, conceptualised as self-efficacy expectancies, perceived control, and cognitive symptom management. The primary outcomes are assumed to be directly influenced by the self-management programme.

Self-efficacy expectancies were assessed by two scales; one is a generic scale, allowing us to compare our results with other studies, whereas the other is a specific scale for cardiac patients, used to improve the sensitivity to change in our study population. General self-efficacy expectancies were measured by the 'General Self-Efficacy Scale' (GSES) [20], which determines the extent to which people believe that they can successfully perform a particular behaviour. Cardiac self-efficacy expectancies were measured using the 'Cardiac Self-Efficacy Questionnaire' [24], which has also been used in other Dutch research among CHF patients [25,26].

Perceived control was assessed by means of the mastery scale developed by Pearlin and Schooler [27]. This scale measures "the extent to which one regards one's life chances as being under one's own control, in contrast to being fatalistically ruled" [27]. The psychometric properties of the Dutch versions of the GSES and the perceived control scale had proved satisfactory in previous studies [21,28,29].

Cognitive symptom management was assessed by the 'Coping with symptoms scale' developed by Lorig and colleagues [30], which measures how often respondents use cognitive symptom management techniques when they feel depressed or experience pain or other unpleasant symptoms. The original 6-item scale was slightly modified into a 5-item scale by omitting the first two items and adding one extra item about the use of breathing techniques as a way to deal with unpleasant symptoms (Elzen et al., evaluation of the CDSMP among chronically ill elderly people in the Netherlands, submitted). Table 2 provides an overview of the outcome variables of the effect evaluation.

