## Methods/Design

### Design

This evaluation study is designed as a two-group randomised controlled trial in which patients are randomly allocated to the intervention or control group (the latter receiving usual care). Data are collected at baseline before the start of the intervention, immediately after the programme (six weeks after the start), and six and twelve months after the start of the programme (see figure 1). Data are gathered by means of self-administered questionnaires and telephone interviews. Various measures are taken to ensure blinding in the data collection process. Questionnaires are collected anonymously and sorted by number. The telephone interviews are conducted independently by trained interviewers, who are unaware to which group patients have been allocated.

For practical reasons, the study consists of eleven consecutive cycles, with one or more CDSMP classes in each cycle. In each cycle, patients are included and randomly allocated to the intervention group or control group. The first cycle started in July 2004 and the final one in September 2005. A total of 21 CDSMP classes (with a parallel control group) were conducted in the period October 2004 – January 2006, in six hospitals. At least two CDSMP classes were conducted in each participating hospital (range 2–6). The Medical Ethics Committee of Maastricht University/University Hospital Maastricht granted approval to conduct this trial. Furthermore, local feasibility of the study design was assessed by each of the local Medical Ethics Committees in the other five participating hospitals.

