### Power calculation

The sample size calculation was based on figures derived from Dutch research among newly diagnosed older CHF patients [21] relating to one of the primary outcome variables in the present study, general self-efficacy expectancies (GSES by Sherer and colleagues [20]). To detect a mean difference of at least 4.0 points in general self-efficacy expectancies between the intervention and control groups (SD = 11.8; equivalent to an effect size of 0.34), at least 137 patients in both the intervention and control groups were required to achieve a power of 80% at an alpha of 0.05 (one-sided). Assuming a drop-out rate of 30% during the trial, a total of 2× 180 patients have to be included in the study.

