### Analysis

Descriptive techniques will be used to characterise the patients participating in the study. Data of the effect evaluation will be analysed according to the intention-to-treat and per-protocol principles. Differences between the intervention and control groups with regard to the primary and secondary outcome variables at the follow-up assessments will be analysed with multivariate techniques adjusting for possible differences in baseline scores and background characteristics. Intervention group patients will be included in the per-protocol analysis if they have attended at least four of the six programme sessions.

Data of the process evaluation will be analysed for patients and leaders by means of descriptive analysis.

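### Four unranked primary scales are compared at three follow-ups under two analysis principles, while the sample size spends the whole 5% alpha on one scale with no time point

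*Protocol article*

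**What the plan says.** All of this is in the protocol article.

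- **Outcomes.** The section on primary outcome variables lists three constructs: "The primary outcomes of the effect evaluation are psychosocial attributes, conceptualised as self-efficacy expectancies, perceived control, and cognitive symptom management". The first has two instruments: "Self-efficacy expectancies were assessed by two scales; one is a generic scale", the other is specific to cardiac patients. "Perceived control was assessed by means of the mastery scale", and cognitive symptom management by a five-item coping scale. That makes four primary scales, with no order among them.
- **Time points.** The Design section sets follow-up "immediately after the programme (six weeks after the start), and six and twelve months after the start of the programme".
- **Analysis.** The Analysis section plans to examine "Differences between the intervention and control groups with regard to the primary and secondary outcome variables at the follow-up assessments". It calls the methods multivariate techniques and has them adjust for baseline scores and background characteristics. No follow-up is singled out. Intention-to-treat and per-protocol are named side by side, without saying which leads.
- **Sample size.** The power calculation uses figures "relating to one of the primary outcome variables in the present study, general self-efficacy expectancies": a difference of 4.0 points, SD 11.8, 80% power and alpha 0.05 labelled one-sided, giving 137 per group. It names no time point and does not divide alpha.

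**The concern.** The only error rate in the article belongs to a single test of a single scale. The design it describes has 4 × 3 = 12 primary comparisons in each analysis set, or 24 over both sets, and nothing in the text says which of them carries the conclusion. If one favourable result among them were taken to show that the programme works, 5% would not be the error rate of that conclusion. The Background says the process analysis may matter for implementation in outpatient care if the programme proves effective. A finding on one scale at one visit, perhaps only among patients who attended at least four sessions, is weak ground for that step.

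**Working it through.** **1. The plan's own figure.** Inputs from the Power calculation section: difference 4.0, SD 11.8, power 80%, alpha 0.05.

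n per group = 2 × SD² × (z_alpha + z_power)² / difference², and 2 × 11.8² / 4.0² = 17.405.

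- Two-sided: 17.405 × (1.960 + 0.842)² = 136.6, so 137. This matches.
- One-sided, as labelled: 17.405 × (1.645 + 0.842)² = 107.6, so 108. This does not match.

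Either way, the full 0.05 goes to one test.

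**2. Count of comparisons.** 2 self-efficacy scales + 1 mastery + 1 coping = 4 scales. 4 scales × 3 follow-ups = 12. 12 × 2 analysis principles = 24.

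**3. Independent tests.** The chance of at least one false positive when there is no effect on any scale is 1 − 0.95^k:

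- k = 4: 18.5%
- k = 12: 46.0%
- k = 24: 70.8%. This is not realistic, because the two analysis sets share most of their patients.

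**4. Correlated tests.** The article gives no correlations, so these are assumptions: 0-0.7 between scales, 0.5-0.8 between visits, and 0.90-0.95 between the intention-to-treat and per-protocol results. The chance of at least one result beyond the 0.05 limit, from a multivariate normal simulation with 200,000 draws per setting, is:

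| Comparisons | One-sided 0.05 | Two-sided 0.05 |
|---|---|---|
| 4 scales, one visit | 12-19% | 13-18% |
| 12, intention-to-treat | 21-40% | 24-42% |
| 24, both principles | 25-50% | 30-53% |

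At 0.5 between scales and 0.7 between visits, the 12 comparisons give 27% one-sided and 32% two-sided.

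**5. What control of alpha costs.** The strictest step of Holm over four scales is 0.05 / 4 = 0.0125. The step 1 formula at that level gives 166 per group one-sided or 195 two-sided, against 137.

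For the patients actually allocated (187 and 131) with the planned 30% drop-out, 130.9 and 91.7 remain. The standard error is 11.8 × √(1/130.9 + 1/91.7) = 1.607, and 4.0 / 1.607 = 2.489. Power without baseline adjustment is then:

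- At 0.05: Φ(2.489 − 1.645) = 80% one-sided; Φ(2.489 − 1.960) = 70% two-sided.
- At 0.0125: Φ(2.489 − 2.241) = 60% one-sided; Φ(2.489 − 2.498) = 50% two-sided.

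These figures use the GSES assumptions; the article gives none for the other scales.

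**The case against.** The strongest objection is scope. This is a condensed article, and a testing order, an alpha split or a leading analysis set may stand in a full protocol or analysis plan that is not shown. That holds: the absence of a multiplicity procedure is not in itself an error here. What remains is what the article does fix, namely an unranked list of primary outcomes and a sample size that gives the whole alpha to one of them. An unseen plan that split alpha over the four scales would no longer fit 137 per group (step 5). One that put GSES first would fit, but the article calls GSES only one of the primary outcomes.

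Second, the article has no rule that any one significant result counts as success. Its aim is to assess effects on several domains. This also holds. A reader might infer that the trial's overall false-positive rate is about 30%, or that a single positive scale at a single visit would be declared a positive trial. The text supports neither. The first needs assumed correlations and an assumed success rule, and 30% is neither the documented rate nor an upper limit. The second is a statement about future reporting.

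Third, the multivariate techniques could be a repeated-measures model with one test per scale, or a joint test. One test per scale brings the figure to 12-19% one-sided, and a joint test over the scales would lower it further. The article describes these techniques as adjustment for baseline and background, not as a global test, but it does not exclude one.

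**Conclusion.** The point holds in conditional form. Four unranked primary scales, three follow-ups, two unranked analysis principles and a full alpha of 0.05 on one scale without a time point are all in the text. If any one nominally significant primary result were read as an effect, the one-sided error rate would be about 12-19% for one visit or one test per scale. For the 12 intention-to-treat comparisons it would be about 21-40%, and 46% under independence. Per-protocol pushes it higher. The ranges rest on the assumed success rule and the assumed correlations. Every setting tried under that rule is well above 5%. The baseline is itself unclear, because the stated sample size matches two-sided 0.05 while the text says one-sided.

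**What to change.** Before follow-up data are complete (January 2007) and before anyone sees results by group, add one paragraph to the analysis section that does four things.

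1. **Name one primary time point.** Twelve months is a natural choice, because patients who announce that they want to stop are asked to complete at least that assessment. Report six weeks and six months as supportive.
2. **Make intention-to-treat the leading analysis**, with per-protocol as supportive.
3. **Control alpha over the four scales at that time point.** One option is to test GSES first, since the sample size is built on it, and then apply Holm to the other three only if GSES succeeds. The other is Holm over all four.
4. **State the sidedness.** Either keep one-sided and explain the 137, or adopt two-sided and say that this departs from the stated text.

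This needs no new patients or measurements. The price is that fewer results can be called confirmatory. Putting GSES first could block the cardiac scale, which the article says was chosen for its sensitivity to change. Holm over all four avoids that but lowers power per scale: at its strictest step, to about 60% one-sided or 50% two-sided for a 4.0-point GSES difference (step 5). Which option to take is the investigators' decision; the defect needs only that one be fixed in advance.

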#### Secondary outcome variables

The outcome measures considered to be indirectly influenced by the programme (secondary outcomes) are health behaviour, quality of life, and health care utilisation (see table 2).

Health behaviour was operationalised into three measurements: (1) smoking and drinking behaviour and Body Mass Index (BMI) (kg/m2), (2) physical activity level, and (3) self-care behaviour. Smoking and drinking behaviour were assessed by asking the patients whether they smoked or drank and in what amounts (i.e. mean number of cigarettes/cigars/pipes smoked per day and mean number of alcoholic drinks per week, respectively). Physical activity level was measured by a modified version of the 'Physical activities scale' developed by Lorig and colleagues [30]. This scale comprises questions about the frequency of walking for exercise, swimming, and bicycling in the preceding month. In addition, respondents were given an opportunity to name alternative exercises in an open-ended question, such as gardening, housekeeping, etc. Finally, CHF-specific self-care behaviour was measured with the 'European Heart Failure Self-Care Behaviour Scale' (EHFScBS), a scale developed in the Netherlands, with good psychometric properties [31].

Quality of life was conceptualised as health-related quality of life, perceived autonomy, and symptoms of anxiety and depression. Health-related quality of life was measured using both generic and disease-specific instruments; the 'RAND 36-item Health Survey' (RAND-36) [32] and the 'Kansas City Cardiomyopathy Questionnaire' (KCCQ) [33]. Perceived autonomy was assessed by one item using a visual analogue scale to measure to what extent the patients were able to arrange their lives the way they would like to (I do not feel I can do so at all – I strongly feel I can do so). Symptoms of anxiety and depression were measured by the 'Hospital Anxiety and Depression Scale' (HADS) [34,35], which is considered to be unbiased by coexisting general medical conditions [36]. The psychometric properties of the Dutch versions of the RAND-36 and the HADS have proved to be satisfactory in previous studies [36,37].

Finally, health care utilisation was measured by patients' self-reports on the number of contacts with a general practitioner, cardiologist, other medical specialist or CHF nurse specialist, the number of hospitalisation days, the reason for hospitalisation, and the number of visits to accident and emergency departments.

#### Covariates

Some additional variables were assessed to characterise the study population and interpret the outcomes of the trial (see table 2). Socio-demographics (gender, age, marital status, living arrangements, education level, and job situation) were assessed at baseline. In addition, two health-related variables were assessed at baseline: co-morbidity using a 19-item checklist of medical conditions [21,38] and cognitive status using the Dutch version of the Telephone Interview for Cognitive Status (TICS) [39,40].

### Measurements in the process evaluation

To determine the feasibility of the programme, four process outcomes were assessed by means of structured evaluation forms: (1) the extent to which the programme was performed according to protocol and the time spent on the sessions, (2) patients' attendance, (3) overall patient adherence and specific adherence with regard to homework assignments, and (4) the opinions of the patients and leaders about the programme. Table 3 presents the outcome variables of the process evaluation.

With regard to compliance with the protocol, the leaders recorded after each session whether they had exceeded specified time limits per activity, skipped, shortened or added parts to activities, or used different training techniques than specified in the protocol. In addition, they recorded preparation time, travel time, time spent on the session, and activities resulting from the session (e.g. answering patients' questions afterwards)

The leaders reported on patient attendance and adherence at group level. Absent patients were phoned by the professional leader to ask for the reason of their absence. Overall adherence (i.e. patients' efforts during the programme sessions) was also assessed at group level, using a 5-point scale (very good – very poor). After completing the programme, both leaders and patients reported on the adherence with regard to homework assignments (e.g. drawing up weekly action plans).

Immediately after the programme, patients who had attended at least three of the six sessions received a structured evaluation form to assess their opinion about the CDSMP. They were asked to what extent they had benefited from the programme (5-point scale; not benefited – benefited very much), and which parts they did or did not appreciate. In addition, patients were asked: (1) to give report marks for the quality of the professional leader and the peer leader, and the programme itself (10-point scale; 1 to 10), (2) whether they would recommend the CDSMP to other CHF patients or to patients with other chronic diseases (e.g. diabetes mellitus), and (3) whether the programme had helped them improve specific health behaviours and coping strategies, compared with the situation before they attended the programme. Finally, the patients were asked to suggest improvements to the CDSMP.

The leaders' opinions about the programme were assessed after each session (report mark on the session, strong and weak points of the session) and after they had completed the programme (report mark on their own skills as leader and questions about the perceived benefits to the patients). At the end of the intervention period (January 2006), all leaders were invited for a structured group interview. During this meeting, the leaders evaluated the feasibility of the protocol in more general terms and made recommendations to improve the CDSMP.

### Data collection

Data for the effect evaluation were collected at baseline and the three follow-up assessments by means of self-administered questionnaires and telephone interviews (see table 2). The telephone interviews were conducted independently by trained interviewers and started two weeks after the questionnaires had been sent out. Patients who announced their intention to stop during the study were asked to complete at least the last follow-up assessment (questionnaire and/or telephone interview).

Data for the process evaluation were collected from the patients by means of self-administered questionnaires. Recording forms and self-administered questionnaires were used to gather data from the CDSMP leaders (see table 3). In addition, bi-monthly structured meetings were held to allow the leaders to discuss their experiences with the various CDSMP classes.

### Power calculation

The sample size calculation was based on figures derived from Dutch research among newly diagnosed older CHF patients [21] relating to one of the primary outcome variables in the present study, general self-efficacy expectancies (GSES by Sherer and colleagues [20]). To detect a mean difference of at least 4.0 points in general self-efficacy expectancies between the intervention and control groups (SD = 11.8; equivalent to an effect size of 0.34), at least 137 patients in both the intervention and control groups were required to achieve a power of 80% at an alpha of 0.05 (one-sided). Assuming a drop-out rate of 30% during the trial, a total of 2× 180 patients have to be included in the study.

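### The 137 patients per group match a two-sided test at 0.05, not the one-sided 0.05 that the power calculation states, so sidedness and sample size must be reconciled

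*Protocol article*

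**What the plan says.** The Power calculation section of the protocol article bases the sample size on one primary outcome, the General Self-Efficacy Scale. The target is stated as "To detect a mean difference of at least 4.0 points in general self-efficacy expectancies", with "SD = 11.8; equivalent to an effect size of 0.34". From this the article concludes that at least "137 patients in both the intervention and control groups were required to achieve a power of 80% at an alpha of 0.05 (one-sided"). With an allowance for 30% drop-out, "a total of 2× 180 patients have to be included in the study".

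The Analysis section describes intention-to-treat and per-protocol comparisons using multivariate techniques that adjust for baseline. It gives neither a significance level nor a sidedness. The power paragraph is therefore the only place in the article that says whether a test is one-sided or two-sided.

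The Discussion (Progress of the study) reports 187 patients allocated to the intervention and 131 to control. It says that the consequences for the power calculation will become clear once data collection ends in January 2007.

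**The concern.** The power paragraph gives the difference, SD, power, alpha, sidedness and resulting sample size, so the result can be checked directly. It fails the check: a one-sided test at 0.05 needs far fewer than 137 per group.

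The required number itself is safe, because 137 is enough under either reading. The error rate is what remains unclear. A sample size of 137 at 80% power implies a critical value of 1.960, which is a 2.5% false-positive rate in favour of the programme. The printed label implies 1.645 and a 5% rate. If the label were followed at analysis, the trial would claim benefit at a looser threshold than the one its size was built for.

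Sidedness also determines how the shortfall in the control group reads, because the two versions give different power for the patients actually recruited.

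**Working it through.** **Inputs**, all from the Power calculation section: difference 4.0; SD 11.8; power 80% (z = 0.842); alpha 0.05; equal groups. The standardised effect is d = 4.0/11.8 = 0.339, so d² = 0.1149. This agrees with the article's 0.34.

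**Formula** (two means, normal approximation): n per group = 2(z_alpha + z_power)²/d².

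**Attempt to reproduce 137:**

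| Test at alpha 0.05 | Calculation | n per group | n by noncentral t |
|---|---|---|---|
| One-sided, as stated | 2(1.645 + 0.842)²/0.1149 = 107.6 | 108 | 109 |
| Two-sided | 2(1.960 + 0.842)²/0.1149 = 136.6 | 137 | 138 |

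With the rounded effect of 0.34, the normal approximation gives 107 one-sided and 136 two-sided. The t-based values are then 108 and 137. The stated 137 exceeds the one-sided answer by 137 − 108 = 29 per group, or 29/108 = 27%. That is too large for rounding.

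**Could another one-sided calculation give 137?**
- Allowing for a Mann-Whitney test gives 113 (efficiency 0.955) to 125 (efficiency 0.864).
- The 59:41 allocation described under Randomisation gives 92 control and about 132 intervention patients.
- To reach 137 per group one-sided at 80% power, the SD would have to be about 13.3 or the difference about 3.5. The article states neither.
- One-sided 0.025 gives 137, but that is the two-sided 0.05 test under another name.

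**Power with 137 per group:** the expected z is 0.339 × √(137/2) = 2.806.
- One-sided: Φ(2.806 − 1.645) = Φ(1.161) = 87.7%.
- Two-sided: Φ(2.806 − 1.960) = Φ(0.846) = 80.1%.

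The stated 80% is therefore true only of the two-sided test.

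**Power with the patients recruited** (187 and 131, from Progress of the study). The expected z is d/√(1/n₁ + 1/n₂). Loss is varied from none to the planned 30%, assumed equal in both arms:

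| Loss per arm | Evaluable | One-sided 0.05 | Two-sided 0.05 |
|---|---|---|---|
| None | 187 and 131 | 90.8% | 84.5% |
| 30% | about 131 and 92 | 80.1% | 70.2% |

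For the last row, the expected z is 0.339/√(1/130.9 + 1/91.7) = 2.489. This gives Φ(0.844) one-sided and Φ(0.529) two-sided.

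**The case against.** The arithmetic is hard to dispute. The fair objections concern what follows from it.

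- **The label is not the decision rule.** It stands only in the power paragraph. The Analysis section is silent on sidedness, and a separate analysis plan may settle it. A reader might infer that the trial will be judged against 1.645. The article does not say so, and the effect on the error rate is conditional. This objection stands.
- **The sample size is not too small because of this.** With 137 evaluable per group, the stated power is reached on either reading. This also stands.
- **The article does not show which element is wrong.** The match to 137 makes the label the likelier slip, but a one-sided test with more patients than it needed cannot be excluded. Changing the label is therefore a recommendation and not a proven correction.
- **A directional hypothesis for self-efficacy is arguable.** One might cite the neutrally worded aims, or the possibility that quality of life or care use worsens, as proof that one-sided testing is wrong. They do not prove it. The Background states a directional assumption about raising self-efficacy, quality of life and care use are secondary outcomes, and the calculation concerns a primary outcome.

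None of this removes the contradiction. The paragraph gives an alpha, a power and a sample size that cannot all be correct, and nothing else in the article reconciles them.

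**Conclusion.** The point holds as an internal contradiction in the Power calculation section. With the stated inputs, one-sided 0.05 needs about 108 per group, and 137 is the two-sided result. At 137 per group, power is about 88% one-sided or 80% two-sided. These results assume a plain comparison of two means with equal groups, and the t-based versions differ by one patient per group.

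If the one-sided label reaches the analysis, the chance of a false claim of benefit is 5% instead of 2.5% per test. That is a possibility the article leaves open and not something it states.

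The choice affects how the recruited sample is described. Under an equal 30% loss in each arm, power is about 80% one-sided but about 70% two-sided. If sidedness is chosen only after the results are known, the choice of threshold could look driven by them.

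**What to change.** Reconcile sidedness and sample size before the follow-up data are analysed.

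- **Preferred:** change one-sided to two-sided in the power paragraph, which reproduces 137, and state that the primary outcomes are tested two-sided at 0.05.
- **If one-sided 0.05 was truly intended:** restate the requirement as about 108 per group, or the power as about 88% at 137, and justify the direction.

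In text, either route costs a word or two in the power paragraph and one sentence. The preferred route also has a statistical cost. The critical value rises from 1.645 to 1.960, and power for the recruited sample is about 70% instead of about 80% under the assumed 30% loss in each arm. The power update promised under Progress of the study should use the chosen sidedness, report this difference, and replace the assumed loss with the observed loss in each arm.

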## Discussion

### Progress of the study

Between July 2004 and November 2005, a total of 717 eligible patients were selected for inclusion from six Heart Failure and/or Cardiology Outpatient Clinics, 339 of whom (47.3%) signed the informed consent form and underwent the baseline assessment (see figure 2). The remaining 378 patients refused or were unable to participate in the study for various reasons: for example, 84 patients did not participate because of physical health problems, 74 patients were not interested or felt no need to participate, and another 74 patients had no time or opportunity to participate (see figure 2). After completion of the baseline assessment, 318 patients were included in the trial; 187 patients were allocated to the intervention group and 131 to the control group.

We had calculated that the study would require a sample size of 2 × 180, including a 30% drop-out rate. A total of 187 patients were allocated to the intervention group, which was according to plan. The number of patients allocated to the control group (n = 131), however, was smaller than planned. At present, follow-up data are being collected. The exact drop-out rate and related consequences for the power calculation will become clear after completion of the data collection in January 2007.

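### The 30% drop-out allowance does not protect the stated 137 per group: 180 per group leaves 126, and the power consequence depends on a sidedness that is itself inconsistent

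*Protocol article*

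**What the plan says.** The Power calculation section of the protocol article builds the sample size in two steps.

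- **Evaluable number.** The target difference on the general self-efficacy scale is 4.0 points ("SD = 11.8; equivalent to an effect size of 0.34"). For 80% power at an alpha of 0.05, labelled one-sided, "at least 137 patients in both the intervention and control groups were required".
- **Inflation for loss.** "Assuming a drop-out rate of 30% during the trial, a total of 2× 180 patients have to be included in the study".

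The Discussion, under Progress of the study, repeats the result: "We had calculated that the study would require a sample size of 2 × 180, including a 30% drop-out rate". It then compares actual allocation with that target. The intervention group, at 187, is described as having met the plan, and the control group, at 131, as having fallen short. It adds that the consequences of the observed drop-out for power will be known once data collection ends.

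**The concern.** The second step does not follow from the first. If 137 is the number that must remain, and 30% of those included are expected to be lost, the number to include is 137 divided by 0.70. The stated 180 is well below that and close to what multiplying by 1.30 would give.

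Two things are at stake. The sample size statement promises an evaluable number that it does not deliver under its own assumption. The same 2 × 180 is also the yardstick for recruitment in the Discussion, and would naturally be the starting point for the later reassessment of power.

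**Working it through.** **Inputs** (Power calculation section unless noted): difference 4.0; SD 11.8; power 80%; alpha 0.05, stated as one-sided; 137 evaluable per group; drop-out 30%; 180 included per group. Allocated: 187 and 131 (Progress of the study). All power figures use the normal approximation.

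**1. Reproducing 137.** The formula is n per group = 2 × [SD × (z for alpha + z for power) / difference]².

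- Two-sided 5%: 2 × [11.8 × (1.960 + 0.842) / 4]² = 136.6, so 137. This is the stated figure exactly.
- One-sided 5%, as labelled: 2 × [11.8 × (1.645 + 0.842) / 4]² = 107.6, so 108 (109 with the t distribution).

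The number 137 therefore belongs to a two-sided test, although the text says one-sided.

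**2. Reproducing 180.**

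- Correct inflation of 137: 137 / (1 − 0.30) = 195.7, so 196 per group, 392 in total. This does not match 180.
- Multiplication: 137 × 1.30 = 178.1, which rounds up to about 180.

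The stated figure appears to come from the multiplication. The article does not give its formula, so this origin is an inference; the mismatch is not.

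**3. What 180 delivers.**

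- Remaining after 30% loss: 180 × 0.70 = 126, which is 137 − 126 = 11 short per group.
- Highest drop-out at which 137 remain: 1 − 137/180 = 23.9%.
- Gap in the inclusion target: 196 − 180 = 16 per group, 32 in total.

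**4. Power with 126 per group.** The standardised difference is 4.0 / [11.8 × √(2/126)] = 2.691.

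- Two-sided 5%: Φ(2.691 − 1.960) = 76.7%.
- One-sided 5%: Φ(2.691 − 1.645) = 85.2%.

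**5. The two consistent versions of the paragraph, both at 80% power.**

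| Test | Evaluable per group | Included per group at 30% loss | Power if 180 per group are included |
|---|---|---|---|
| Two-sided 5% | 137 | 196 | 76.7% |
| One-sided 5% | 108 | 108/0.70 = 154.3, so 155 | 85.2% |

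**6. Effect on the benchmark in the Discussion.**

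| Benchmark per group | Intervention (187) | Control (131) |
|---|---|---|
| 180, as stated | 7 above | 49 short |
| 196, two-sided | 9 short | 65 short |
| 155, one-sided | 32 above | 24 short |

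The control group is short on every version. The intervention group is short only on the two-sided one.

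**The case against.** The arithmetic of the drop-out step is hard to dispute. The article gives no other definition of drop-out and no separate allowance, and the Discussion confirms that the 30% is already inside the 2 × 180. The serious objections concern what follows from it.

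- **A reader might infer that 196 per group was needed outright and that the design fell below 80% power.** The document does not support that. It states a one-sided alpha, under which 108 evaluable and 155 included would suffice, and 180 is more than enough. The figure 196 holds only if 137 is kept as the requirement, which in effect means a two-sided test that the article never states. This objection stands. It does not rescue the paragraph, because 180 still fails to protect the 137 that the paragraph demands, and one inconsistency that offsets another does not make the text right.
- **Might 180 have been derived some other way?** By coincidence, 126 is also the one-sided requirement for 85% power, and 126/0.70 = 180. But the section states 80% power and 137 patients, so this cannot be its derivation as written. It is a further reason to call the multiplication by 1.30 likely rather than certain.
- **A reader might infer that the Discussion misreports recruitment when it says the intervention group met the plan.** It does not. The sentence compares 187 with the 180 actually planned, and that comparison is correct. It makes no claim that 137 will remain.
- **The inflation error is not what limits this trial.** This also stands. The control group, at 131, is below 137 before any loss. With 30% loss from the actual allocation (130.9 and 91.7 remaining), power is about 70% two-sided or 80% one-sided, whichever inclusion target had been written down. The Data collection section also describes an effort to obtain the last assessment from patients who intend to stop, so evaluable loss may turn out below 30%.

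**Conclusion.** The drop-out allowance is wrong relative to the plan's own requirement. At 30% loss, 180 per group gives 126 evaluable patients, not 137. Keeping 137 would take 196 per group, and 180 suffices only up to 23.9% loss. This rests on nothing but the stated 137, 30% and 180.

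The power consequence is conditional. If the test is two-sided, the planned power at 30% loss is about 77% instead of 80%, a loss of about 3 points. If it is one-sided, as labelled, there is no loss: 126 evaluable give about 85%. Both figures assume the stated difference and SD, equal groups and the normal approximation. Because the paragraph pairs a two-sided number with a one-sided label, the two inconsistencies have to be settled together.

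Severity is minor to moderate. A stated sample size is wrong and is repeated as a benchmark, but no analysis or endpoint depends on it.

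**What to change.** Do not enrol more patients. State in the Power calculation section which test applies, and restate the paragraph to match it:

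- **If two-sided 5%:** remove the one-sided label. Say that 137 evaluable per group requires 196 per group (392 in total) at 30% drop-out, and that the 180 per group used gives 126 evaluable and about 77% power at that rate, or protects 137 up to 23.9% drop-out.
- **If one-sided 5%:** replace 137 by 108. Say that this requires 155 per group at 30% drop-out, and that the 180 per group used gives 126 evaluable and about 85% power.

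The sidedness should be the one fixed for the trial's analysis, not the one that gives the better power figure, and it should be settled before results are seen.

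In Progress of the study, correct the sentence that presents 2 × 180 as already including 30% drop-out. The comparison of 187 and 131 with the planned 180 may stay as a record of recruitment, but the matching benchmark (196 or 155) should be given beside it. The promised reassessment of power should start from the same test and from the actual, unequal group sizes.

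The cost is wording in two places. Nothing in data collection changes, and the stated planning power becomes slightly less favourable only on the two-sided version.
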